### Participant eligibility and recruitment procedures

For this pragmatic pilot trial, inclusion and exclusion criteria were selected to reflect clinical care in the UW Post-COVID Rehabilitation and Recovery Clinic and to maximize generalizability such that a broad range of patients with long COVID engaged in care in a similar multidisciplinary clinic would be represented. Inclusion criteria are that participants must be at least 18 years of age; reside in the state; have a long COVID diagnosis; be able to read, speak, and understand English; and have reliable telephone and Internet access. Exclusion criteria are severe cognitive impairment as evidenced by two or more errors on the 6-item cognitive screener [28] and current participation in other psychosocial treatment primarily for a long COVID symptom(s) or problem(s).

The UW Post-COVID Rehabilitation and Recovery Clinic serves as the recruitment site. Prospective participants are identified through the wait-list for the existing telemedicine group self-management intervention. Prospective participants are sent an approach letter via email or physical mailing that indicates why they are being approached and how study staff received their name and contact information. Study staff call prospective participants within 1 week after sending the approach letter. Interested patients may also contact research staff directly after receiving the approach letter. Prospective participants may also be identified and referred to the study by providers who are already referring patients to the telemedicine group-based self-management intervention.

### Screening and baseline assessments

The study coordinator provides a brief description of the study to prospective participants over the phone. Prospective participants who are interested in enrolling in the study are then screened for eligibility (see inclusion/exclusion criteria above). Eligible prospective participants complete the informed consent process to enroll into the study. Following enrollment, participants are asked to confirm their availability for upcoming self-management groups which are scheduled based on provider availability. If participants are available for the upcoming group schedule, participants complete a brief reassessment of eligibility, confirming that they have not participated in any other similar self-management programs targeting post-COVID symptoms. Within 2 weeks of the group’s Session 1 date, participants are randomly assigned to the intervention group or the wait-list control group. If availability is not confirmed, the study coordinator contacts the participants to confirm availability for the next group(s), as soon as that schedule is available from the clinic. Following randomization, participants complete a battery of self-report baseline measures. See Table 1 for study schedule and outcome measures. Study data are collected and managed using REDCap electronic data capture tools hosted at the UW [29, 30].

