Self-management interventions equip and empower people with chronic health conditions and/or disability to actively manage their symptoms by providing them with strategies that they can use in their day-to-day lives [10, 11]. For example, these strategies may include pacing and energy conservation to reduce or manage fatigue and pain, practicing breathing exercises to improve shortness of breath and related anxiety, applying attention strategies to improve cognition, using cognitive behavioral techniques to change unhelpful patterns of thinking, enlisting social support to improve coping, engaging in goal-directed behavior aligned with values to improve mood, participating in mindfulness and relaxation practices to reduce stress and support mood, and improving sleep hygiene to optimize sleep, to name a few [12]. Furthermore, telemedicine is a viable platform for delivering self-management interventions [13]. Telemedicine is convenient, accessible, and cost-effective, has high patient satisfaction ratings, and reduces the risk for transmission of COVID-19 [14–16].

The mixed-methods randomized controlled trial (RCT) described here was developed in response to the critical need to advance research on effective psychosocial rehabilitation for adults with long COVID. We describe a pragmatic, randomized two-group parallel design to examine the feasibility, acceptability, and appropriateness and explore the preliminary efficacy of a 6-week telemedicine self-management group intervention for adults with long COVID. The self-management intervention will be compared to a wait-list control condition (delayed treatment) because there is currently no standard rehabilitation intervention for adults with long COVID.

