** Secondary outcomes**			
Depression Short Form 8b** [21]		X	X
Anxiety Short Form 8a** [21]		X	X
Fatigue Short Form 8a** [21]		X	X
Sleep Disturbance Short Form 8a** [21]		X	X
Cognitive Function — Abilities Short Form 8a** [21]		X	X
Self-Efficacy for Managing Chronic Conditions — Managing Symptoms Short Form 8a** [21]		X	X
Ability to Participate in Social Roles and Activities Short Form 8a** [21]		X	X
Pain Interference Short Form 8a** [21]		X	X
Long COVID symptom and impact tools [22]		X	X
Credibility/expectancy questionnaire [23]		X*	
Patient Global Impression of Change scale [24]			X*

^*^Completed by intervention participants only

**Patient-Reported Outcomes Measurement Information System (PROMIS)

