### Randomization and procedures to minimize bias

Participants are randomized using a 1:1 randomization to treatment versus wait-list control condition system. When participants confirm availability for an upcoming clinic group schedule and are confirmed eligible following the re-assessment of Eligibility, participants are 1:1 randomized to either the treatment experimental condition or wait-list control condition. The order of randomization is determined by the order in which participants chronologically completed the re-assessment of eligibility. To minimize bias, the clinicians delivering the intervention are blinded to the research participation status of their group members, as some group members will be enrolled in the study while others will not be. In addition, the REDCap system automatically sends participants baseline and post-treatment/wait-list survey links, where the participant can directly enter their data. As a result, the potential for study staff biases to interfere with data collection is avoided.

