### Data collection procedures and measures

Participants complete self-report measures via REDCap at baseline (prior to starting the treatment/wait-list period) and at post-treatment/wait-list after completing the six-session intervention group or 6-week wait period. For data capture and storage, this study uses REDCap, a secure, password-protected, and HIPAA compliant web-based data platform hosted by the UW Institute of Translational Health Sciences [29, 30].

The primary and secondary outcomes are listed in Table 1. Primary outcomes include the Feasibility of Intervention Measure (FIM), Acceptability of Intervention Measure (AIM), and Intervention Appropriateness Measure (IAM) [20]. Each measure consists of four items that are rated on a 5-point ordinal scale assessing the degree to which an intervention is feasible (e.g., “this intervention seems doable”), agreeable (e.g., “I like this intervention”), or appropriate (e.g., “this intervention seems fitting”). A score greater than 3 (“neither agree nor disagree”) will be used as the cutoff for a dichotomous rating of feasibility, acceptability, and appropriateness. The FIM, AIM, and IAM have shown excellent reliability as well as substantive and discriminant content validity [20]. Secondary outcomes include Patient-Reported Outcomes Measurement Information System (PROMIS) measures of fatigue, sleep disturbance, cognitive difficulties, self-efficacy, pain interference, depression and anxiety symptoms [21], and a long COVID symptom and impact tools measure [22] and Patient Global Impression of Change scale [24].

In addition, participants randomized to the self-management intervention (*n* = 25) complete a 45-minute semi-structured interview with research staff within one month after the final session. The interviewer queries participants about the feasibility, acceptability, and appropriateness of the intervention as well as suggestions for improving the intervention across these areas. Participants are also asked about the perceived efficacy of the intervention and how the intervention could be improved to increase efficacy. Last, the interviewer queries participants’ impressions of the intervention workbook and elicit suggestions for improvement. Data is transcribed via Rev, a secure online transcription service [31].

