### Statistical analysis plan

An intent-to-treat (ITT) approach will be used for all quantitative analyses. If participants are missing data at the individual-item level of a multi-item scale, we will impute the missing data using the within-group mean scores for the scale; however, a score will not be imputed if the participant is missing ≥ 40% data in a scale.

First, we will compute descriptive statistics to characterize the sample in terms of demographic and condition-related factors. To assess the first study aim, we will calculate the means and standard deviations of the AIM, IAM, and FIM and quantify the proportion of participants who rate the intervention as feasible, acceptable, and appropriate (average score greater than 3). We will quantify adherence as the percentage of sessions attended out of six sessions. These statistics will be used to contextualize the qualitative results and help inform the extent of modifications necessary to improve the feasibility, acceptability, and appropriateness of the intervention for adults with long COVID.

The second study aim to examine intervention effects is exploratory. We will determine whether randomization was successful by using *t*-tests and chi-square tests to compare the intervention and wait-list groups on a variety of demographic and baseline outcome variables. Any variables that differ between the groups will be included as covariates in the subsequent regression models. After examining randomization, we will explore intervention effects. For the second aim, we will conduct linear regression to assess intervention effects on each outcome (nine models) and will covary for the baseline level of the outcome variable, intervention credibility/expectancy [23], age, sex, and race.

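### Self-reported baseline outcomes are collected after randomization, very probably with the arm known, and then serve as balance check and covariate in the exploratory efficacy models

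*Protocol article*

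**What the plan says.** In the section Screening and baseline assessments, the sequence is consent, a check of availability for the next group, and a short re-check of eligibility. Then, within two weeks of the first session, "participants are randomly assigned to the intervention group or the wait-list control group". The next step for a randomized participant is given as "Following randomization, participants complete a battery of self-report baseline measures".

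Table 1 has the same order. Screening and consent stand in the Enrollment column, and every baseline instrument stands in the Allocation column. One of these, the credibility/expectancy questionnaire, carries the footnote "Completed by intervention participants only".

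The section Data collection procedures and measures describes completion "at baseline (prior to starting the treatment/wait-list period", which fixes baseline relative to the start of the study period but not relative to randomization.

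On masking, the section Randomization and procedures to minimize bias says that "the clinicians delivering the intervention are blinded to the research participation status of their group members". It adds that survey links are sent automatically, as protection against staff influence. It says nothing about masking participants. The Introduction describes the comparator as delayed treatment.

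The section Statistical analysis plan uses the baseline outcomes twice. They enter t-tests and chi-square tests of whether randomization succeeded, and any variable found to differ becomes a covariate. The nine linear regressions of the second aim also "will covary for the baseline level of the outcome variable", along with credibility/expectancy, age, sex and race.

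**The concern.** A baseline covariate is safe to adjust for because allocation cannot have influenced it. Here that protection is missing. Prospective participants come mainly from the waiting list for this same program, with provider referral as a second route. On allocation they learn either that they start shortly or that they wait again, and they then rate depression, anxiety, fatigue, sleep, self-efficacy and related states. Such ratings can respond to the news.

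If they do, two things follow. The balance tests may show a difference caused by allocation, which the plan would read as chance imbalance and adjust for. The regression would also subtract part of that artificial difference from the estimated effect. Once the data are in, a baseline taken after disclosure cannot be separated into true level and reaction.

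**Working it through.** The protocol gives no figure on this point, so there is none to reproduce. The check is first of the order of steps, then of what a shift would do.

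**Order.** Screening and baseline assessments and Table 1 both put baseline after randomization. The timing statement in Data collection procedures and measures is compatible with this, since a survey can precede the first session and still follow randomization. No section reverses the order.

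**Knowledge of the arm.** No sentence says when participants are told. Three facts point to knowledge at baseline: a delayed-treatment comparator is hard to conceal this close to the first session; the baseline battery itself differs by arm through the intervention-only questionnaire; and no participant masking or delayed release of allocation is described.

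**Bias formula.** Write the adjusted estimate as (Y1 − Y0) − b(X1 − X0), where Y and X are arm means at follow-up and baseline, arm 1 is the intervention, and b is the within-arm slope. If allocation shifts the baseline contrast by d, the estimate changes by −b × d. The documents give neither b nor d, so both are assumptions, in SD units. Size of the bias:

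| Slope b | d = 0.1 | d = 0.2 | d = 0.3 |
|---|---|---|---|
| 0.5 | 0.05 | 0.10 | 0.15 |
| 0.6 | 0.06 | 0.12 | 0.18 |
| 0.7 | 0.07 | 0.14 | 0.21 |

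**Direction.** Take a scale on which higher is worse. If wait-listed participants rate themselves worse on learning that they must wait, d is negative and the bias works against the intervention. If intervention participants rate themselves worse, d is positive and the bias favours it.

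**Simulation.** There were 4,000 runs per setting, with no true effect, two-sided 5% tests, baseline as the only covariate, and a constant shift affecting baseline only. The arm sizes are 25 (50 randomized 1:1) and 20 (the protocol's completers per arm). In these units the pre-post correlation equals the slope b.

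| Per arm | b | d | Mean bias (SD) | Outcome test rejects | Baseline t-test flags |
|---|---|---|---|---|---|
| 25 | 0.5 | 0 | 0.001 | 5.4% | 5.0% |
| 25 | 0.5 | 0.2 | −0.101 | 7.1% | 11.0% |
| 25 | 0.5 | 0.3 | −0.148 | 9.0% | 18.3% |
| 25 | 0.7 | 0 | 0.004 | 4.8% | 4.3% |
| 25 | 0.7 | 0.2 | −0.143 | 10.9% | 10.0% |
| 25 | 0.7 | 0.3 | −0.209 | 16.8% | 17.4% |
| 20 | 0.5 | 0 | 0.002 | 5.0% | 5.0% |
| 20 | 0.5 | 0.2 | −0.095 | 6.3% | 10.3% |
| 20 | 0.5 | 0.3 | −0.142 | 7.8% | 15.5% |
| 20 | 0.7 | 0 | −0.004 | 4.8% | 5.0% |
| 20 | 0.7 | 0.2 | −0.142 | 9.2% | 9.5% |
| 20 | 0.7 | 0.3 | −0.208 | 14.2% | 15.4% |

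The simulated bias matches −b × d. The d = 0 rows represent baseline before allocation: bias is about zero and both tests are near their nominal 5%.

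**The case against.** The strongest reply is that little of importance is at risk. The second aim is labelled exploratory, and the Discussion says that the sample suits exploration and not a fully powered evaluation. The primary measures (FIM, AIM, IAM) are taken only after treatment and only in the intervention arm. Attendance and the interviews use no baseline, and allocation cannot alter demographics. All of this stands and limits the point.

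The bias is also modest beside the noise. With slope 0.6 and 20 per arm, the standard error of the adjusted difference is about √((1 − 0.36) × 2/20) = 0.25 SD, so the central value of 0.12 SD is about half a standard error. At slope 0.7 the standard error is √(0.51 × 2/20) = 0.23 SD, and the largest bias considered, 0.21 SD, is still below it. This bears on urgency. It does not make the order sound, because a larger trial that kept this order would keep the bias while its standard error shrank.

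A reader might infer three stronger things that the documents do not support:

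- That the protocol says participants know their arm at baseline. It states only the order; disclosure is a strong inference.
- That every efficacy estimate is biased. The estimates can be biased if ratings react to allocation, and neither the size nor the sign of any reaction can be derived from the text.
- That losses between randomization and baseline will differ by arm and break the intent-to-treat principle. Differential loss is speculative, and the handling of a wholly missing baseline may be set out in a full analysis plan that is not shown.

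**Conclusion.** The point holds for the exploratory second aim. The order of randomization and baseline is explicit and nowhere contradicted, and the resulting scores are used both in the randomization check and as covariates. Under assumed slopes of 0.5 to 0.7 and allocation-induced shifts of 0.1 to 0.3 SD, the baseline-adjusted estimates would be off by 0.05 to 0.21 SD, in the direction opposite to the shift and otherwise unknown. For shifts of 0.2 to 0.3 SD, a baseline t-test would flag imbalance in roughly 10% to 18% of trials instead of 5%. These figures rest on a uniform shift and on participants knowing their arm, which is very probable but not stated.

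**What to change.** Have participants complete the eight PROMIS measures and the long COVID symptom and impact tools at the eligibility re-assessment, and release the allocation only once they are submitted. Move these rows of Table 1 to a pre-allocation column and revise the sentence in Screening and baseline assessments to match. Keep the credibility/expectancy questionnaire after allocation as a separate step, since only intervention participants complete it. The cost is a changed order of steps, a modification to the IRB, and a few people who complete baseline and are never randomized.

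The Trial status section reports recruitment from January 2023 and expects treatment to end in January 2024, so the new order helps only those not yet randomized. For participants already randomized, report by arm when baseline was completed relative to disclosure and how many baselines are missing. Add a sensitivity analysis that does not adjust for the post-randomization baseline outcome, nor for any other self-reported baseline score that the balance tests flag. Its price is precision: at slope 0.6 and 20 per arm, the standard error rises from 0.25 to √(2/20) = 0.32 SD. Excluding participants by survey timestamp is not a workable substitute. Under the stated order every baseline follows randomization, so such a rule could remove nearly everyone.

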### Self-management intervention

Rehabilitation psychologists at the UW and the VA Puget Sound Health Care System developed a six-session group self-management intervention for patients with long COVID. These groups are currently offered to patients receiving care in the UW Post-COVID Rehabilitation and Recovery Clinic. This intervention teaches participants behavioral strategies known to be helpful in managing symptoms in patient populations with similar symptom profiles as long COVID (e.g., myalgic encephalomyelitis, multiple sclerosis), including fatigue, memory and attention problems, insomnia, dyspnea, coping with anxiety and uncertainty, and stress management [14, 15]. See Table 2 for a description of intervention content by session. The intervention is delivered via telemedicine by licensed rehabilitation psychologists. The rehabilitation psychologists follow the treatment manual and cover the major components of each session, which are highlighted with fidelity statements. Fidelity statements are bolded in the treatment manual and help ensure that the rehabilitation psychologists are covering the essential content. An example of a fidelity statement is “To ensure fidelity say something like the following: ‘In this group, we will apply the biopsychosocial model to many of your symptoms to identify factors that may contribute to the presence of your symptoms as well as to understand and apply strategies to improve your symptoms or how you cope with your symptoms’”). The rehabilitation psychologists meet monthly for case consultation via video conference.

**Table 2 Tab2:** Major components of the manualized self-management intervention for long COVID

Session	Session content
1	*Introduction to long COVID and the biopsychosocial model* Information and discussion on the following: long COVID and related symptoms, biopsychosocial model and self-management philosophy, and dyspnea Skill: diaphragmatic breathing
2	*Energy management* Information and discussion on the following: long COVID fatigue, cycle of deconditioning, assessing and reestablishing priorities Skill: pacing for energy management
3	*Enhancing sleep, memory, and attention* Information and discussion on the following: sleep problems, memory and attention difficulties Skill: sleep hygiene and strategies to improve attention
4	*Anxiety and coping with uncertainty* Information and discussion on the following: anxiety and emotional responses to COVID-19 and long COVID, discernment for effective coping, mindfulness Skill: coping with controllable and uncontrollable stressors, grounding mindfulness exercise
5	*Stress management* Information and discussion on the following: stress associated with long COVID, cognitive behavioral model, and related strategies to enhance coping with stress Skill: thought challenging, coping thoughts
6	*Enhancing communication* Information and discussion on the following: effective communication with healthcare providers for long COVID care, communication with family and friends about long COVID and symptom management, effective goal setting Skill: communication strategies, goal setting that is specific, measurable, achievable, relevant, time-bound (SMART)

### Randomization and procedures to minimize bias

Participants are randomized using a 1:1 randomization to treatment versus wait-list control condition system. When participants confirm availability for an upcoming clinic group schedule and are confirmed eligible following the re-assessment of Eligibility, participants are 1:1 randomized to either the treatment experimental condition or wait-list control condition. The order of randomization is determined by the order in which participants chronologically completed the re-assessment of eligibility. To minimize bias, the clinicians delivering the intervention are blinded to the research participation status of their group members, as some group members will be enrolled in the study while others will not be. In addition, the REDCap system automatically sends participants baseline and post-treatment/wait-list survey links, where the participant can directly enter their data. As a result, the potential for study staff biases to interfere with data collection is avoided.

